### 2.14. Sample size calculation

Since no previous similar study was conducted, the sample size was determined via the G*Power version 3.1.9.4 software calculation, based on a large effect for a two-tailed *t* test. The calculation showed that a total of 26 patients were needed. However, to account for a 15% patient drop-out expected frequency. For 80% power with an effect size of 0.8, a total of 60 patients were required, with 30 patients in each group.

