## 1. Introduction

Esophagus cancer’s new cases in 2020 were 604,100, the 10th most common cancer in the world. Esophagus cancer also had an astonishing 544,076 new deaths in 2020, which represents 5.5 percent of all cancer mortality.^[1,2]^ Based on the current trend the forecast for the burden of esophagus cancer is expecting an increase to 739,666 new cases and 723,466 deaths in 2030, and 987,723 new cases and 914,304 deaths in 2040.^[2]^ Not long ago, the 5 years survival for esophageal cancer was 21.7% (United States data from 2011–2019).^[3]^ Esophagus cancer patients often suffer from progressive dysphagia due to the tumor and its effect on the integrity and function of the esophagus, which leads to serious weight loss and possible malnourishment.^[4]^ A study on 154 French hospital wards found that 60.2% of the patients with esophagus and/or stomach cancer were malnourished.^[5]^ In a study including 1482 esophageal cancer patients existing prevalence of malnutrition was around 50% of the patients, when measured by the NRS-2002.^[6]^ Advanced esophagus cancer patients have a limited oral feeding ability and their nutrition support is often provided through a jejunostomy tube feeding. Especially at the time of preoperative chemotherapy and radiotherapy sessions.^[7,8]^ In clinical observation of patients after jejunostomy, the presence of dumping syndrome was observed, due to the faster speed at which the food enters the intestine through the jejunostomy tube.^[9]^ The prevalence of dumping syndrome is considered high among esophagus cancer patients, with a prevalence ranging between 20-50% of the patients.^[10,11]^ Dumping syndrome is a condition in which the food is rapidly introduced into the intestine at a rate that is faster than normal, this usually occurs due to anatomical and physiological changes in the digestive system. Dumping syndrome’s main symptom is diarrhea, other symptoms contain abdominal cramps, nausea, and vasoactive symptoms like tachycardia, palpitations, fatigue, a desire to lie down following eating, pallor, diaphoresis, lightheadedness, hypotension, headache, and syncope.^[12,13]^ This often occurs 1 hour after a meal although late dumping can occur 1 to 3 hours after a meal.^[12,14]^ After the food rapidly enters the intestine a large number of hormones are secreted, such as neurostatin, vasoactive intestinal peptide, incretins, insulin, and glucagon which cause the vasomotor symptoms to appear.^[14]^ Dumping syndrome is also associated with weight loss.^[15,16]^ This is particularly important for esophagus cancer patients due to their initial high risk of malnourishment.^[5]^ The management of dumping syndrome in Western medicine is mainly based on dietary adjustments.^[16]^

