### 2.12. Outcome measures

Main outcome measurements are: body weight, BMI (will be measured weekly) dumping syndrome questioners: the Sigstad’s score in order to determine the diagnosis of dumping syndrome and the Arts’ dumping questionnaire in order to assess early or late dumping syndrome (will be measured on the baseline, week 3, week 6) (see Figure S1, Supplemental Digital Content, http://links.lww.com/MD/J34 for the Sigstad’s score and Figure S2, Supplemental Digital Content, http://links.lww.com/MD/J35 for the Arts’ dumping questionnaire).

The secondary outcomes are: muscle grip strength test (measured weekly in kg) (by electronic hand grip test model EH101 manufactured by “CAMRY,” China), blood test: Complete Blood Count, kidney and electrolytes (measured as adjuvant adjuvant concurrent chemoradiation therapy schedule), pre-albumin, albumin level, glucose blood levels, inflammation data including Erythrocyte Sedimentation Rate and C-reactive protein (measured at baseline and on week 6). Total Intensive care unit stay, total hospital stay, and total mechanical ventilation in days will be measured 6 months after inclusion. Mortality will be measured at 3 months, 6 months. Medical charts and drug use will also be measured (Fig. 4). All measurements will be measured by nurses and doctors in the department that are blind to the study group allocation.

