### 2.16. Statistical analysis

The statistical analysis for all measurements will analyze changes from baseline and changes over time. Categorical data will be presented as a percentage (n %), while continuous data will be presented as mean ± standard deviation. For changes from baseline the paired *t* test will be used. The independent *t* test or the Mann–Whitney *U* test will analyze continuous variables depending on applicability, and the Chi-square test or Fisher’s exact test (as appropriate) will be used for categorical variables. For repeat measurements data the repeat measures ANOVA will be used. The IBM SPSS Statistics version 22.0 (SPSS Inc, Chicago, IL) will be used for data analysis, and significance will be determined at a *P* value < .05. If applicable, a subgroup analysis will be done on tumor stage, age, BMI, dumping syndrome status at baseline and dumping syndrome type. If there are any missing data, they will be imputed using multiple imputations (if applicable).

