Limitations of the study include a specific Taiwanese population and cannot be generalized to other populations. This study is also only a single-center study. The study protocol could not apply a double-blind design due to the type of intervention (manual acupuncture). The study will investigate the role of acupuncture in the prevention of dumping syndrome and malnourishment, the study does not require a positive Sigstad’s score to verify dumping syndrome as a condition for inclusion, therefore it is possible that the number of patients that will develop dumping syndrome could be low, in this case, the study will focus on body weight and BMI as the main outcomes to assess the prevention of malnourishment. The study did not specify the cancer stage in the inclusion criteria. High mortality rates in Esophagus cancer might impair the completeness of the data and can increase the levels of missing data.

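### The stated 80% power covers only a comparison of means; the protocol leaves open whether dumping is tested as a score or as a diagnosis, and a diagnosis would have much less power

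*Protocol article*

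**What the plan says.** Section 2.14 bases the sample size on one calculation, "based on a large effect for a two-tailed *t* test", and concludes: "For 80% power with an effect size of 0.8, a total of 60 patients were required, with 30 patients in each group". It does not say which outcome the effect size belongs to.

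Section 2.12 lists four main outcomes: body weight, BMI, the Sigstad score and the Arts questionnaire. The last two are taken at baseline, week 3 and week 6. The purpose given for the first of these is classification: "the Sigstad’s score in order to determine the diagnosis of dumping syndrome". The Arts questionnaire is there to separate early from late dumping. Section 2.1 states the aim as preventing and treating dumping syndrome. The limitations paragraph in section 3 says that "it is possible that the number of patients that will develop dumping syndrome could be low", and that in this case body weight and BMI become the focus.

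Section 2.16 gives the t test or Mann-Whitney test for continuous variables and repeated measures ANOVA for repeated measurements. For the rest, "the Chi-square test or Fisher’s exact test (as appropriate) will be used for categorical variables". No outcome is named beside any of these tests, and no adjustment for the baseline value is mentioned.

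**The concern.** A t test at d = 0.8 supports a difference in means and nothing else. The trial's hypothesis concerns dumping syndrome, and the protocol often describes dumping as a state that a patient has or develops. Analysed that way, the comparison is between two proportions. Cutting a score at a diagnostic threshold discards information, so the same underlying effect and the same number of patients give less power.

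As written, either analysis could be chosen and only one has the advertised power. At stake is how a null result is read: a non-significant difference in diagnosis rate could be taken as coming from a test with 80% power, when no calculation in the protocol supports that. The choice between score and diagnosis would also stay open until the data are seen.

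**Working it through.** **Inputs from the protocol.** Two-tailed t test, effect size 0.8, power 80%, 15% drop-out (2.14). Allocation 1:1 (2.1). Significance level 0.05, taken from 2.16 ("significance will be determined at a *P* value < .05") because 2.14 gives none of its own. Dumping rate from section 1: "with a prevalence ranging between 20-50% of the patients". This is a background figure, not a design input.

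**Step 1: reproduce the plan's figure.** For an independent two-sample t test with n per arm, power comes from the noncentral t distribution with 2n − 2 degrees of freedom and noncentrality d√(n/2).

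- n = 26: noncentrality 0.8 × √13 = 2.88, critical value 2.01, power 80.7%.
- n = 25: power 79.1%, so 26 per arm is the smallest number that reaches 80%.
- 26 × 2 = 52; 52 × 1.15 = 59.8, giving 60.
- n = 30: noncentrality 0.8 × √15 = 3.10, power 86.1%.

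The 60 reproduces. On the way the text says "The calculation showed that a total of 26 patients were needed", but 26 is the number per arm: a total of 26 (13 per arm) has about 50% power. That is a separate wording point and does not change the 60. With a Mann-Whitney test (relative efficiency 0.955 under normality), power is about 79% at 26 per arm. A numeric score therefore has close to the stated power under either test for continuous data.

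**Step 2: the same effect, analysed as a diagnosis.** The protocol gives no rate for the acupuncture arm, so two assumptions are needed:

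- (a) the score behaves as a normal variable that acupuncture shifts down by 0.8 SD;
- (b) the diagnostic cut-off lies where the control rate equals a value p in the background range of 20-50%.

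The acupuncture rate is then Φ(Φ⁻¹(p) − 0.8). For p = 50% this is Φ(−0.8) = 21.2%. Exact power is the sum of the binomial probabilities of all pairs of counts that give P < .05 (chi-square without continuity correction, or Fisher).

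| Control rate | Acupuncture rate | Chi-square, 26 / 30 per arm | Fisher, 26 / 30 per arm |
|---|---|---|---|
| 20% | 5.0% | 40% / 45% | 22% / 24% |
| 35% | 11.8% | 54% / 58% | 39% / 46% |
| 50% | 21.2% | 61% / 65% | 50% / 55% |

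The full range is 22% to 65%. By the normal approximation, 80% power under these assumptions would need 76 per arm at a control rate of 20% and 43 per arm at 50%.

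**Step 3: what a chi-square test could detect.** From a control rate of 50%:

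- 26 per arm (52 evaluable): 50% v 15% has 81% power.
- 30 per arm: 50% v 16% has 82% power, and 50% v 17% has 79%.

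**Step 4: sensitivity to assumption (a).** If 0.8 is read as Cohen's h, a standardized difference between proportions, then with 26-30 per arm chi-square power is about 76-87% and Fisher power about 41-81%. The shortfall for chi-square largely disappears under that reading. However, 2.14 specifies a t test, for which 0.8 is a difference in SD units, so the latent shift is the more direct translation.

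**The case against.** The strongest reply is that the protocol does not make dumping a binary endpoint. The main outcomes are listed as a score and a questionnaire, measured three times. Section 2.16 opens by saying that all measurements are analysed as changes from baseline and over time, which suits a numeric score. The sentence on chi-square and Fisher is generic, and mortality would need it anyway. Describing what an instrument is for does not fix the form of the endpoint. Two of the four main outcomes are plainly continuous, and if few patients develop dumping the protocol moves its focus to exactly those two.

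All of this stands. A reader might infer from 2.12 and 2.16 together that dumping is defined as a diagnosis and assigned to chi-square or Fisher; no sentence says so. A reader might also infer from the power table that a real effect would be missed more often than not over most of the 20-50% range. That does not hold either: chi-square power is 54-65% at control rates of 35% and 50%. If Fisher is used only when an expected count falls below 5, power reaches 50% at a control rate of about 30% with 30 per arm. Only Fisher used throughout is at or below about 50% for most of the range.

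The choice between score and cut-off can also be left to a full analysis plan. What the objection does not remove is that this document prints a power figure without an outcome, describes the titular condition largely in diagnostic and occurrence terms, and allows two analyses of which only one has that power.

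**Conclusion.** The point holds as an ambiguity with a measurable cost, not as a proven mismatch between test and outcome. The stated 80% is right for a comparison of means at d = 0.8. It does not carry over to a comparison of diagnosis rates, where power would be about 22-65% with 26-30 per arm. That range depends on the 0.8 SD latent shift and on using a background prevalence as the week-6 control rate, and it should be quoted only with both assumptions attached. The protocol does not show which analysis the investigators intend. The numeric reading fits 2.16 at least as well, so confirming it should be easy.

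**What to change.** - **2.12 and 2.16:** name the between-arm difference in the numeric Sigstad score at week 6, adjusted for the baseline score, as the tested dumping comparison. The baseline score is already collected, and adjusting for it usually adds precision when it correlates with the week-6 score. Report the diagnosis rate and the early/late type as supportive results, as risk differences with 95% confidence intervals.
- **2.14:** state that the 80% power applies to a continuous comparison at d = 0.8 and not to the diagnosis rate. If a detectable difference in rates is quoted, tie it to the number analysed: for chi-square from a 50% control rate, about 50% v 15% with 26 per arm (52 evaluable), or about 50% v 16% with 30 per arm.

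The cost is wording in three sections, with no new patients or measurements. The downside is that the diagnosis rate, which clinicians may find easier to interpret, becomes a supportive result.

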## 2. Methods

### 2.1. Study design and settings

This single-blind randomized control trial will be implemented in the Department of thoracic surgery of China medical university hospital (CMUH), Taichung City, Taiwan. The study will be initiated on February 2023 and will be concluded until January 2025. This single center study will use a 1:1 ratio parallel group allocation. Informed consent will be obtained prior to the patient’s enrollment. The 2 groups are an intervention group (INT) and a control group (CON). The study was approved by the institutional review board (IRB) of CMUH (approval no. CMUH111-REC3-004) and a study protocol registration online on https://clinicaltrials.gov/ct2/show/NCT05801666 (registration no. NCT05801666). The study aims to examine the effect of acupuncture on preventing and treating dumping syndrome in esophagus cancer patients after feeding jejunostomy surgery. The study will also measure the effect of acupuncture on preventing malnutrition using body weight and body mass index (BMI) (see Fig. 1). In this study, both the patients and the assessors of outcome measurements will be blinded to the group’s allocation.

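### The sample-size paragraph gives the per-group requirement of 26 as the total; the planned 60 still stands, but the printed steps do not lead to it

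*Protocol article*

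**What the plan says.** Section 2.14 (Sample size calculation) describes a G*Power calculation "based on a large effect for a two-tailed *t* test" and gives its result: "The calculation showed that a total of 26 patients were needed". An unfinished sentence follows, which sets out "to account for a 15% patient drop-out expected frequency" but does not say what was done with that percentage. The paragraph ends: "For 80% power with an effect size of 0.8, a total of 60 patients were required, with 30 patients in each group".

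The other inputs are in other sections. Section 2.1 says "This single center study will use a 1:1 ratio parallel group allocation", and section 2.16 says "significance will be determined at a *P* value < .05". The size of 60, with 30 per group, also appears in the Abstract (Methods) and in section 2.2. Section 2.7 describes 60 sealed envelopes, and section 2.8 repeats the total of 60. Section 2.14 does not say that 26 is a per-group figure, and the number 52 appears nowhere in the article.

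**The concern.** Taken literally, the paragraph says that 26 patients in all are enough for the stated power, and then that 60 are required for the same effect size. The only step between the two figures is a 15% drop-out allowance, which cannot turn 26 into 60. That would take a loss of 1 − 26/60 = 57%.

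This paragraph is the only justification of trial size in the article. The figure that matters later is the number of evaluable patients needed. The limitations paragraph of section 3 warns that high mortality may leave the data incomplete, so the number of evaluable patients may well fall below 60. Someone judging a shortfall against the printed 26 would use a threshold half the size it should be.

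**Working it through.** **Inputs.** Two-tailed t test, effect size d = 0.8, 80% power, 15% drop-out, stated results 26 and 60 (section 2.14); 1:1 parallel groups (section 2.1); significance level 0.05 (section 2.16). I assume that the t test is the independent two-sample test, as the design implies.

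**Method.** For groups of n₁ and n₂, the test statistic follows a noncentral t distribution with n₁ + n₂ − 2 degrees of freedom and noncentrality d × √(n₁n₂/(n₁ + n₂)). Power is the probability that it falls beyond the two-sided 5% critical values.

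**Step 1: the stated 26.** The normal approximation gives n per group = 2 × (1.96 + 0.84)²/0.8² = 2 × 7.84/0.64 = 24.5, so 25. The exact calculation gives 25.5, so 26 per group and 52 in total. The printed 26 is therefore reproduced as a per-group number but not as a total.

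**Step 2: power at the sizes in question (d = 0.8, two-sided 5%).**

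| Evaluable patients | Noncentrality | Power |
|---|---|---|
| 13 + 13 = 26 | 0.8 × √6.5 = 2.04 | 49.9% |
| 25 + 26 = 51 | 0.8 × √12.745 = 2.86 | 79.9% |
| 26 + 26 = 52 | 0.8 × √13 = 2.88 | 80.7% |
| 30 + 30 = 60 | 0.8 × √15 = 3.10 | 86.1% |

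With 13 per group, 80% power is reached only at d of about 1.15.

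**Step 3: does another standard reading give 26 as a total?**
- One-sided two-sample test, 80% power: 21 per group, 42 in total.
- Paired or one-sample two-sided test: 15 patients at 80% power, 23 at 95%.
- Two-sided two-sample test at 85%, 90% and 95% power: 60, 68 and 84 in total.

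None of these gives 26.

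**Step 4: from 26 to 60.**
- 26 read as a total: 26 × 1.15 = 29.9, so 30; or 26/0.85 = 30.6, so 31. Neither is 60.
- 26 read as per group: 26 × 1.15 = 29.9, so 30 per group and 60 in total. This matches the plan and is probably the route taken, although the article does not show it.
- Dividing by the retained fraction instead: 52/0.85 = 61.2, so 62 in total (31 per group).

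**Step 5: what 60 delivers.** 60 × 0.85 = 51 evaluable patients, against 52 required; power is 79.9%. With no loss it is 86.1%.

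**The case against.** The best defence is that only one intermediate number is mislabelled. The operative size is 60, it is stated consistently throughout the article, and it supports the claim of 80% power. Nothing in the article suggests that the trial could stop at 26. The article also condenses a fuller protocol, so the calculation that the ethics board read is unknown. All of this stands, and it limits the weight of the point. It does not remove it, because the article states a wrong number in a complete sentence; this is not a detail left to another document.

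Three stronger readings are tempting, and the documents support none of them.

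- *The trial is underpowered.* It is not on its own assumptions: power at 60 is 86.1% with no loss and 79.9% with 15% lost.
- *The 60 is too small because multiplying by 1.15 is the wrong inflation, and 62 are needed.* The arithmetic is right, but the shortfall is one evaluable patient (51 against 52), and 79.9% rounds to the claimed 80%. The 15% is an expectation, not an upper limit. Counting every drop-out as lost is also pessimistic: section 2.6 keeps the data of withdrawn patients who agree, and section 2.16 plans multiple imputation where applicable.
- *Relying on 26 would halve the power.* Power would fall from about 80% to about 50%, a relative loss of about 38% (30.1/80).

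**Conclusion.** The point holds as the correction of a stated figure. Section 2.14 labels the per-group result as the total, so the stated requirement is too low by a factor of two (26 instead of 52) and the printed steps do not lead to 60. The planned enrolment of 60 is not in question.

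This rests on the protocol's own effect size of 0.8, an independent two-sample t test at a two-sided 5% level, equal groups and 15% drop-out. Whether d = 0.8 is realistic is a separate matter, not examined here. That 60 was derived from 26 × 1.15 per group is an inference, though the only route tried that links the two printed numbers and the drop-out rate.

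**What to change.** In section 2.14, replace the total of 26 with 26 evaluable patients per group (52 in total), giving 80.7% power for d = 0.8 with a two-sided t test at the 5% level. Complete the drop-out sentence. Suggested wording: *Sixty patients (30 per group) will be randomised; with 15% drop-out about 51 remain evaluable, which gives about 80% power.*

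The new text should not say that the calculation serves a single primary comparison. Section 2.12 lists four main outcomes (body weight, BMI, Sigstad's score and the Arts' questionnaire) and does not single one out, so such wording would add something the protocol does not define.

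The cost is one paragraph of text. Enrolment, allocation and analysis are unchanged.

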### 2.15. Data management

To ensure the accuracy and reliability of data, patient data will be uploaded to the CMU hospital electronic database, along with manually written reports on measurements that are not usually uploaded to the system. The manually written report will be stored in a secure location in the office of the principal investigator and is scheduled to be destroyed 5 years post trial completion. The principal investigator will also arrange meetings with study staff to ensure the patients’ enrollment and interventions are according to the study protocol.

### 2.16. Statistical analysis

The statistical analysis for all measurements will analyze changes from baseline and changes over time. Categorical data will be presented as a percentage (n %), while continuous data will be presented as mean ± standard deviation. For changes from baseline the paired *t* test will be used. The independent *t* test or the Mann–Whitney *U* test will analyze continuous variables depending on applicability, and the Chi-square test or Fisher’s exact test (as appropriate) will be used for categorical variables. For repeat measurements data the repeat measures ANOVA will be used. The IBM SPSS Statistics version 22.0 (SPSS Inc, Chicago, IL) will be used for data analysis, and significance will be determined at a *P* value < .05. If applicable, a subgroup analysis will be done on tumor stage, age, BMI, dumping syndrome status at baseline and dumping syndrome type. If there are any missing data, they will be imputed using multiple imputations (if applicable).

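### No deciding time point or repeated-measures effect is fixed for any main outcome, so each has several candidate tests at P < .05 and the stated 80% power belongs to none of them

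*Protocol article*

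**What the plan says.** Section 2.12 makes body weight, BMI, the Sigstad score and the Arts questionnaire the main outcomes. Weight and BMI are taken weekly; the two dumping instruments "will be measured on the baseline, week 3, week 6". No visit is marked as the primary one.

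Section 2.16 opens: "The statistical analysis for all measurements will analyze changes from baseline and changes over time". It assigns paired t tests to changes from baseline and independent t or Mann–Whitney tests to continuous variables. It then adds: "For repeat measurements data the repeat measures ANOVA will be used". The one threshold is "significance will be determined at a *P* value < .05".

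Section 2.14 bases the sample size on a large effect for a two-tailed t test and concludes: "For 80% power with an effect size of 0.8, a total of 60 patients were required". It names neither an outcome nor a time for the effect size.

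**The concern.** The issue lies within a single outcome and would remain if one primary outcome were named. For one dumping score, the week-3 comparison, the week-6 comparison, the ANOVA group effect and the ANOVA group-by-time effect could each be presented as the result. They answer different questions and can disagree on the same data. If the choice is made after the results are known, the false-positive rate for that outcome exceeds 5%.

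The sizing does not settle the choice. A t test needs one value per patient, whereas section 2.16 sends repeated data to ANOVA, and every main outcome is repeated. One of the ANOVA effects, the group effect, averages over all visits including baseline, where randomised arms have no treatment difference. It is therefore a diluted version of the end-of-treatment difference and need not have the stated power.

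**Working it through.** **Inputs from the article.** Two-sided 0.05 (2.14, 2.16); d = 0.8, 80% power, 15% dropout, 30 per group (2.14); baseline, week 3 and week 6 for the dumping scores, weekly for weight and BMI (2.12).

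**Assumptions, because the article gives no figures.** Continuous, normally distributed outcomes with equal SDs, scaled to 1; 26 analysed per arm; baseline plus weeks 1 to 6 for the weekly outcomes (7 occasions); compound symmetry with between-visit correlation ρ, and also AR(1) for the weight false-positive rates.

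**The plan's own figure.** A two-sample t test at d = 0.8, two-sided 0.05, needs 26 per arm (exact power 80.7%), so 52 in total. 52 × 1.15 = 59.8, giving 60; dividing by 0.85 instead gives 61.2, or 62 in even groups. The 60 reproduces to within two patients. The 26 that section 2.14 calls a total is a per-arm figure (13 per arm would give 50% power). That is a separate slip and plays no part in what follows.

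**False positives within one outcome, no true effect (simulation).**

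| Outcome | Between-group tests counted | Chance of at least one P < .05 |
|---|---|---|
| Dumping score, ρ 0.3–0.7 | ANOVA group and group-by-time only | about 9–10% |
| Dumping score, ρ 0.3–0.7 | those two plus week-3 and week-6 change | about 14–15% |
| Weight, ρ 0.5–0.9 | the two ANOVA effects plus six weekly changes | about 22–27% |

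The first row agrees with 1 − 0.95² = 9.75%, since the two ANOVA effects are close to independent under the null. Within-group paired tests are not counted, because they do not compare the arms.

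**Power of the ANOVA group effect.** With T occasions the standardised effect is the mean of the visit effects divided by √[(1 + (T − 1)ρ)/T]. Example: three visits, effects 0, 0.4 and 0.8, ρ = 0.5. The mean is 0.4, the divisor is √(2/3) = 0.816 and the ratio is 0.49. With 26 per arm that gives 41% power.

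| Occasions | Time course to d = 0.8 at week 6 | Group-effect power, ρ from 0.3 to 0.9 |
|---|---|---|
| 3 | linear build-up | 49% down to 31% |
| 3 | full effect from week 3 | 73% down to 50% |
| 3 | effect only at week 6 | 25% down to 16% |
| 7 | linear build-up | 61% down to 32% |
| 7 | full effect from week 1 | 97% down to 72% |

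For comparison, a week-6 t test has 81% whatever the earlier course. With linear build-up over three visits, a week-3 t test (d = 0.4) has 29%, and the group-by-time effect has 57% at ρ = 0.3, 72% at 0.5 and 92% at 0.7.

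**Power of a baseline-adjusted week-6 contrast.** The effective d is 0.8/√(1 − ρ²). At ρ = 0.3 this is 0.8/√0.91 = 0.839, power 84%; at ρ = 0.7 it is 0.8/√0.51 = 1.120, power 98%.

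**The case against.** The strongest reply is that section 2.16 can be read more narrowly. All main outcomes are repeated, so all go to ANOVA; the independent t and Mann–Whitney tests then serve single-valued variables such as hospital days; and changes from baseline go to a within-group paired test. On that reading only two between-group candidates remain. The point stands in part: the false-positive rate is then about 9–10%, not 14–15%. It still leaves open which ANOVA effect decides, and neither is the t test for which the trial was sized.

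A second reply is that this is a condensed article and an unseen analysis plan may settle the matter. That would be fair if the article were silent. It instead sets competing tests side by side at one threshold and powers the trial for a contrast it does not locate in time. The decision rule is badly fixed rather than merely left out.

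A third reply is that the calculations treat the scores as continuous, while section 2.12 uses the Sigstad score to determine a diagnosis, and that six weekly comparisons are inferred from the word weekly. Both are correct and both are assumptions here.

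A reader might also infer that the trial has only about half its stated power, or that a true d of 0.8 would more often than not be missed. The article does not support that. Nothing in it says the group effect will judge efficacy, and the figure near 41% needs a linear build-up and a correlation near 0.5, neither of which is given. With full effect from week 3 the group effect has 50–73%; for weekly outcomes with full effect from week 1 it has 72–97%.

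**Conclusion.** The concern holds in this form: for each main outcome the article fixes neither the deciding visit nor the repeated-measures effect that tests efficacy, and its d of 0.8 is attached to no time point. Under the stated assumptions, free choice among the between-group tests raises the false-positive rate for a single dumping score from 5% to about 9–10% on the narrow reading and about 14–15% on the wider one. For weight it is about 22–27% if six weekly comparisons count.

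For the three-visit scores the ANOVA group effect falls short of 80% power under every time course tried, but by how much depends on quantities the article does not supply. The defensible statement on power is that the 80% has no definite meaning until the contrast is named. The point should be corrected, but it does not invalidate the design. Multiplicity across the four main outcomes is a separate matter and is not addressed here.

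**What to change.** Add to section 2.16: *For each main outcome the deciding contrast is the acupuncture-minus-sham difference at week 6, adjusted for the baseline value (ANCOVA, or a model with the post-baseline visits as outcomes and baseline as a covariate), at two-sided 0.05. Week 3, the other weekly values, within-group paired tests and the time profile are supportive and are reported as estimates with 95% confidence intervals. The ANOVA group effect that includes baseline is not used as the efficacy test.*

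Add to section 2.14 that d = 0.8 refers to this week-6 contrast. Week 6 is the end of the treatment course and is already in the measurement schedule of every main outcome, so no visit or patient is added. With 26 per arm and a baseline correlation of 0.3 to 0.7, the adjusted contrast has 84–98% power at d = 0.8.

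The cost is wording, plus one real concession: an effect seen only at week 3 becomes supportive evidence. The change should be made and dated before any comparison by arm is seen.
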